## Abstract

**Introduction:**

Due to its greater generation of muscle strength and less metabolic demand, eccentric exercise has been widely used in rehabilitation and for improving physical fitness. However, eccentric exercise can induce muscle damage by providing structural changes and reduced muscle function, so even with the protection caused by the repeated bout effect from eccentric exercise, it is necessary to seek alternatives to reduce this damage caused by stress. Thus, ischemic preconditioning could represent an aid to reduce the damage muscle or increase the protective effect caused by eccentric exercise.

**Objectives:**

To compare the effects of ischemic preconditioning, using different occlusion pressures, on acute and delayed responses to perceptual outcomes, markers of muscle damage, and performance in post-eccentric exercise recovery.

**Methods:**

A randomized controlled placebo clinical trial will be carried out with 80 healthy men aged 18 to 35 years who will be randomly divided into four groups: ischemic preconditioning using total occlusion pressure, ischemic preconditoning with 40% more than total occlusion pressure, placebo (10 mmHg), and control. The ischemic preconditioning protocol will consist of four cycles of ischemia and reperfusion of five minutes each. All groups will perform an eccentric exercise protocol, and assessments will be carried out before, immediately after, and 24, 48, 72, and 96 h after the end of the eccentric exercise to evaluate creatine kinase, blood lactate, perception of recovery using the Likert scale, being sequentially evaluated, pain by the visual analog scale, pain threshold using a pressure algometer, muscle thickness by ultrasound, muscle tone, stiffness and elasticity by myotonometry, vectors of cell integrity through electrical bioimpedance, and maximal voluntary isometric contraction using the isokinetic dynamometer. The trial was registered at ClinicalTrials.gov (NCT04420819).

**Discussion:**

The present study aims to present an alternative technique to reduce muscle damage caused by eccentric exercise, which is easy to apply and low cost. If the benefits are proven, ischemic preconditioning could be used in any clinical practice that aims to minimize the damage caused by exercise, presenting an advance in the prescription of eccentric exercise and directly impacting on the results of post-exercise recovery.

**Trial registration:**

ClinicalTrials.gov NCT04420819. Registered on 19 May 2020; Last update 24 March 2021.

**Supplementary Information:**

The online version contains supplementary material available at 10.1186/s13063-021-05285-7.

## Introduction

Resistance training is the most commonly used training method for maintaining and improving strength and muscle mass [1], being characterized by concentric or eccentric muscle contractions [2, 3]. Evidence indicates that eccentric training programs have been widely used in musculoskeletal rehabilitation or for improving physical fitness [4, 5]. The lower metabolic demand makes eccentric exercise (EE) an alternative to obtain better hypertrophic adaptations when compared to concentric exercise, promoting a greater amount of strength [2, 6, 7].

Thus, this exercise presents an interesting alternative for clinical use and should be encouraged in the rehabilitation process, to improve performance and prevent injuries. However, it must be considered that EE produces marked acute responses, structural damage, and reduced muscle function [8]. Due to the high force exerted on these deformable units, deformation occurs, which causes muscle stiffness, and may influence the risk of injuries [9].

Exercise-induced muscle damage (EIMD) is characterized by morphological alterations, decreased performance with reduced range of motion and strength, edema, delayed-onset muscle pain, and muscle proteins in the blood, especially creatine kinase (CK).

The literature has pointed out that EE itself has a protective effect against muscle damage; however, there are also strategies to assist recovery, such as massage, photobiomodulation, cryotherapy, and compressive clothing [10–15]. Some pre-exercise strategies are also used as a way to minimize these damages, especially ischemic preconditioning (IPC) [16], which is characterized by the application of short periods of circulatory occlusion (ischemia) and reperfusion of a limb in the minutes or hours preceding the exercise, through insufflations and deflations of a pressure cuff [17, 18].

The IPC was first presented by Murry et al. [17] and applied to the musculoskeletal system by Takarada et al. [19] and consists of three to four cycles of ischemia and reperfusion with 5 min of ischemia and reperfusion varying from 3 to 5 min [17, 19]. Patterson et al. demonstrated that this strategy can be administered from one to two times a day, applying three to five cycles of ischemia and reperfusion, with 5 min of ischemia and reperfusion varying from 3 to 5 min [20].

This strategy has been considered attractive, because in addition to being low-cost and non-invasive, it has easy clinical applicability and provides an ergogenic aid to improve physical performance [18]. Recent studies have emphasized the effectiveness of IPC in assisting post-exercise recovery [21], which can reduce the damage caused by ischemia-reperfusion injury after EIMD. These ischemia-reperfusion injuries cause metabolic and contractile damage similar to those presented in the EIMD, thus causing an increase in the concentrations of intracellular calcium, and in the appearance of muscle proteins in the blood and cytokine markers such as lactate and CK [22, 23].

Thus, its application before exercise can reduce the magnitude of muscle damage and subsequent pre-inflammatory responses, directly stimulating the body’s physiological defense system and improving tissue integrity [16, 24]. Therefore, some form of post-exercise recovery measurement is required, which can be acquired through a Likert recovery perception scale that ranges from 0 to 10 [25].

However, studies have been trying to determine the best prescription parameters for this strategy. Cocking et al. [26] and Lindsay et al. [27] analyzed the IPC response dose. The first study [26] investigated whether different IPC protocols improve muscle endurance, with a four-cycle and an eight-cycle protocol. The results showed that the four-cycle protocol demonstrated an improvement in resistance performance compared to the eight-cycle protocol. The second study [27], on the other hand, examined whether IPC applied different numbers of times per day improves performance; however, daily frequency was not a determining factor for improving performance [26, 27]. Another factor that hypothetically can determine the results of IPC is the pressure of occlusion generated in the period of ischemia; however, no studies were found that analyzed these effects in the recovery period after an EIMD.

Based on the above, it is hypothesized that IPC will provide a protective effect against eccentric EIMD, reducing muscle pain and improving clinical indicators, without, however, impairing muscle function. In addition, these responses are expected to be more evident in the higher occlusion pressure since there is a greater increase in blood flow and high levels of post-ischemic adenosine. In addition, factors related to the IPC response dose may influence responses in post-exercise recovery. Therefore, the aim of the present study is to compare the effects of IPC, using different occlusion pressures, on acute and delayed responses to perceptual outcomes, markers of muscle damage, and performance in post-eccentric exercise recovery.

## Methods

### Study design

This is a single-blind, placebo-controlled, clinical trial, with four parallel groups conducted at the Center for Studies and Care in Physiotherapy and Rehabilitation at Universidade Estadual Paulista (FCT/UNESP), Presidente Prudente, SP, Brazil. The trial was registered at ClinicalTrials.gov (NCT04420819) and approved by the Research Ethics Committee of FCT/UNESP, Presidente Prudente, SP, Brazil (CAAE: 30765020.3.0000.5402). Informed consent form is available from the corresponding author on request.

On the consent form, participants will be asked if they agree to use of their data should they choose to withdraw from the trial. Participants will also be asked for permission for the research team to share relevant data with people from the Universities taking part in the research or from regulatory authorities, where relevant. This trial does involve collecting biological specimens for storage.

The study protocol follows the SPIRIT 2013 checklist (Standard Protocol Items: Recommendations for International Trials) [28] (Supplementary File 1) and the TIDieR (Template for Intervention Description and Replication) [29], so that the information and quality of reports of interventions are well described [30].

### Participants and population analysis

For this study, the sample will consist of 80 healthy male individuals, aged between 18 and 35 years. We chose to investigate only men due to the differences found in the level of muscle strength and power between the sexes [31, 32]. These participants will be recruited, will be recruited from a database of the Sports Physiotherapy Laboratory of FCT/UNESP and the community, through dissemination posters on the institution’s premises, social networks, and advertisements in the local media. These procedures are recommended by Treweek et al. [33] as strategies to improve participant recruitment.

Individuals who exhibit one or more of the following characteristics will not be included (1) the presence of any health condition that contraindicates or prevents EE; (2) diabetes and diagnosed arterial hypertension; (3) inflammatory, psychiatric, cardiovascular, and/or respiratory rheumatological disease; (4) being an alcoholic, using drugs, and/or being a smoker; (5) history of knee surgery (for example, meniscal repair and ligament reconstruction) or recent musculoskeletal injury to the lower limbs that may impair performance during tests or interventions (for example, muscle injury, tendinopathy, patellofemoral pain in the lower limbs, and/or back pain in the previous six months); (6) involvement in any type of training program during the study period; (7) engaging in a lower limb strength training program during the three months prior to participating in the study; (8) use of ergogenic supplements to improve physical performance and/or muscle mass and/or vasoactive drugs; and (9) having one or more risk factors predisposing to thromboembolism [34].

Participants will be excluded from the study if they: present any health problem that does not allow continuity, use medication, electrotherapy, or other therapeutic means that may interfere with any result, perform unusual or strenuous physical activities during the evaluation period, or wish to leave the study.

Participants will be instructed in advance not to perform any physical activity or to use any therapeutic form of pain relief or performance improvement during the data collection. In addition, the participant may experience pain, dizziness, and sweating common to the practice of exercise, if there are episodes of musculoskeletal injuries, individualized physiotherapeutic treatment will be offered.

The flowchart of the study design and the composition of the groups is illustrated in Fig. 1.

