#### Sample calculation

The sample calculation was performed based on the study by Bailey et al. [54], using the CK variable, since this variable expresses the amount of muscle protein in the blood representative of indirect muscle damage. The G*Power 3.1.9.7 software was used. Considering the standard deviation in the CK concentration of 200 μL, using a two-tailed hypothesis test with 80% test power and 5% significance level, a sample size of 16 participants per group was stipulated. Predicting sample loss, 4 participants per group were added totaling 80 participants. To increase the participants’ adherence to the intervention, telephone contact will be made daily to encourage them to remain in the study, and thus avoid losses. In case of discontinuity or withdrawal, the intention to treat will be used.

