### Statistical analysis

The normality of the data will be verified by the Kolmogorov Smirnov test. If normality is detected, the sample characterization variables will be presented as mean and standard deviation, if not, as median and interquartile range. To compare the characterization of the sample, one-way ANOVA with Tukey’s post test or Kruskal-Wallis with Dunn’s post test will be used depending on the normality of the data.

The comparisons of the outcomes between the four groups studied and the moments will be performed using the technique of analysis of variance for repeated measures model in the two-factor scheme, which will provide information on the effects of time, group, and interaction. The repeated measurement data will be checked for sphericity violation using Mauchly’s test and the Greenhouse-Geisser correction will be used when the sphericity is violated. For moment analysis, Bonferroni’s post-test for parametric distribution or Dunn’s post test for non-parametric distribution will be used and the analysis between the groups will be performed using one-way ANOVA or the Kruskal-Wallis test.

In addition, the effects of the groups studied will be verified for all the outcomes assessed by calculating the effect size (ES) using Cohen’s *d*, considered as “null” (< 0.2), “small” (≥ 0.2), “moderate” (≥ 0.6), “large” (≥ 1.2), or “very large” (≥ 2.0) [55].

An intention-to-treat analysis will be performed using the patient’s most recent assessment in case of withdrawals or absence of data. The level of significance will be p < 0.05 for all tests. The statistical program SPSS (version 24.0) (SPSS Inc., Chicago, IL, USA) will be used for the analyses.

The external evaluator will enter the data into the database for screening, randomization, and statistical analysis purposes. Double data entry in electronic format will be used. Data integrity will be monitored by regularly scrutinizing data files for omissions and errors. Participants will be given an anonymous study ID to protect confidentiality, and only study investigators will have access to the final trial data set. The spreadsheets containing the raw numeric data of the data generated in this study will be stored in its entirety initially on two external hard drives and two online clouds. Any data required to support the protocol can be supplied on request.

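### Randomised participants are excluded for interfering medication, therapy or strenuous activity after exercise, which contradicts the intention-to-treat promise or leaves it nominal

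*Protocol article*

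**What the plan says.** The section Participants and population analysis lists the eligibility criteria first. A separate list then follows: "Participants will be excluded from the study if they: present any health problem that does not allow continuity, use medication, electrotherapy". The medication and therapy grounds are limited to means that could affect a result. The list ends with those who "perform unusual or strenuous physical activities during the evaluation period, or wish to leave the study".

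The same section tells participants not to exercise and not "to use any therapeutic form of pain relief or performance improvement during the data collection". It also says that "if there are episodes of musculoskeletal injuries, individualized physiotherapeutic treatment will be offered".

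Two other sections deal with those who leave. Sample calculation says: "In case of discontinuity or withdrawal, the intention to treat will be used". Statistical analysis describes an intention-to-treat analysis that uses the participant's "most recent assessment in case of withdrawals or absence of data". The Discussion counts the intention-to-treat approach among the study's strengths.

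No section says whether a participant excluded for medication, therapy or activity still attends the remaining visits, or whether that participant's data enter the analysis.

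**The concern.** Assessments run to 96 h after the eccentric exercise, so the exclusion grounds operate after randomisation and after the intervention. Some of them are plausibly consequences of the outcome. The exercise is meant to cause muscle damage and soreness, and a sore participant is more likely to take pain relief or seek therapy. The Introduction expects ischemic preconditioning to act by "reducing muscle pain and improving clinical indicators", and pain is a secondary outcome. If that hypothesis is true, exclusions for pain relief will be more frequent in the placebo and control arms. The Randomization section adds that participants are not blind to allocation, which may also influence who seeks relief.

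At stake is the comparability that randomisation provides. Exclusion for behaviour that follows the outcome makes the missing data informative, and here the loss is avoidable because the visits are already scheduled.

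**Working it through.** **The plan's own figures.** Sample calculation gives 16 per group plus 4 for losses. 16 + 4 = 20 and 4 × 20 = 80, as stated. The allowance is 4/20 = 20% for losses of every kind. No CK difference is stated. Back-solving from 16 per group, 80% power, two-sided 5% and a two-group t-test gives 1.02 SD. That figure is derived, concerns CK only, and is not a yardstick for a bias in soreness.

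**The two readings of the exclusion rule.**

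| Reading | What happens to an excluded participant | Consequence |
|---|---|---|
| Dropped from the analysis | Not counted in the randomised arm | Contradicts Sample calculation and Statistical analysis |
| Follow-up stops, last value carried forward | Counted, but later visits are filled with an earlier value | Intention-to-treat in name only; the value may precede peak damage |

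Muscle thickness, a primary outcome, shows the second reading most clearly. The outcomes section says that ultrasound is not done immediately after exercise (the second Study design section is less clear on this). On that basis, a participant excluded before the 24 h scan would have the pre-exercise thickness carried to 96 h, which records no swelling.

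**Illustration 1: dropped, one arm only.** Assumptions not in the document: a normal outcome, exactly the sorest fraction q of one arm deleted, the other arms untouched. The shift in that arm's mean is −φ(z)/(1 − q), where z is the upper q point.

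- q = 0.05: 0.1031/0.95 = 0.11 SD
- q = 0.10: 0.1755/0.90 = 0.19 SD
- q = 0.20: 0.2800/0.80 = 0.35 SD

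**Illustration 2: both readings, removals in both arms.** Assumptions, again not in the document: participants are removed when soreness passes a threshold that catches 10% or 20% of controls; the treatment effect is the same on soreness and outcome; their correlation is 0 to 0.9; the carried-forward value is 40% of the peak value, with a mean rise of 2 SD in controls.

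| True effect | Removed, control vs active | Effect if dropped | Effect if carried forward |
|---|---|---|---|
| 0.5 SD | 10% vs 4%, or 20% vs 9% | 0.34–0.50 SD | 0.28–0.42 SD |
| 1.0 SD | 10% vs 1%, or 20% vs 3% | 0.75–1.00 SD | 0.67–0.89 SD |

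Hand check of one carried-forward cell (true effect 0.5, correlation 0, 20% vs 9% removed). Control mean: 2 − 0.6 × 0.20 × 2 = 1.76. Active mean: 1.5 − 0.6 × 0.09 × 1.5 = 1.42. The difference is 0.34 against a true 0.50.

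Under these assumptions the effect shrinks on both readings, except when participants are dropped and soreness is unrelated to the outcome; then there is no bias. Other removal patterns would give other sizes and could reverse the direction.

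**The case against.** A reader might infer that the exclusion rule and intention-to-treat cannot both be followed, so that the promise is defeated outright. The document does not support that. A wish to leave stands in the same list as medication and activity, so the list can be read as grounds for discontinuation. Statistical analysis then supplies a value for withdrawals and absent data, and the consent form asks about use of data after withdrawal. On that reading everyone stays in the analysis as randomised. This stands: the contradiction is firm only if excluded participants are dropped. What remains on the other reading is that measurable outcomes are discarded and replaced.

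A reader might also infer that all the exclusions track greater soreness. This is plausible for pain relief and therapy but remains an inference. For activity it may run the other way, since less sore participants may be the more active. Some medication use will have nothing to do with soreness.

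The rule is narrower than a ban on all medication or activity, and the advance instructions should make such events less frequent. No rate is given. Illustration 1 is a worst case: it deletes exactly the sorest people, in one arm only, and its 20% case borrows an allowance meant for losses of all kinds. It also does not describe carrying values forward.

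Finally, a wish to leave and a health problem that makes testing unsafe are legitimate reasons to stop assessments. Only interfering medication or therapy and strenuous activity are in dispute.

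**Conclusion.** The point holds on either reading. The plan excludes randomised participants for post-randomisation events, at least one of which, pain relief, is plausibly related to outcome and arm. Either this contradicts the intention-to-treat promise, or it reduces that promise to filling in values that could have been measured. The trial's own offer of physiotherapy could also meet the exclusion rule, which adds to the need to reconcile the sections.

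The size and direction of the bias are unknown. The 0.11 to 0.35 SD shift in one arm and the shrinkage in the second illustration rest wholly on assumed inputs and show only that the bias need not be trivial. This should be corrected, but nothing in the document shows how often it would arise.

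**What to change.** For interfering medication, therapy and strenuous activity, replace exclusion from the study by recording a protocol deviation, with its type and time. Continue the scheduled assessments to 96 h unless consent is withdrawn or testing is unsafe. Analyse all participants as randomised using their observed values, and use a per-protocol set without these participants only as a sensitivity analysis. Amend Participants and population analysis, Sample calculation and Statistical analysis together so that they agree on who is followed and who is analysed, including anyone who receives the physiotherapy offered. The instruction to avoid pain relief and the offer of physiotherapy need not change for this purpose.

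The cost is revised wording, a short deviation log, and the notice to the ethics committee and registry update that the Randomization section already requires for changes. No visits are added and the total stays at 80. The downside is that some observed values will include effects of medication, therapy or activity; the log and the sensitivity analysis let a reader judge how much that matters.

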**Fig. 1 Fig1:**
[figure not shown]
Flowchart of the study design. Legend: IPC-TOP (ischemic preconditioning with total occlusion pressure); IPC-40% (ischemic preconditioning with 40% higher pressure is to be applied than the closure pressure); IPC-10 mmHg (preconditioning with 10 mmHg)

### Randomization

The randomization sequence will be developed by a researcher who will not be involved in recruiting, evaluating, or training participants using software (Microsoft Office Excel 2007) and will be placed in sequential numbering in opaque and sealed envelopes. There will be blinding of the evaluators and statistical analysis procedures. The experimental protocol will be supervised by trained physiotherapists who are not involved in the randomization process or assessments. Due to the nature of the interventions, the participants who perform the exercise will not be blind to the allocation of the groups. There is a Trial Steering Committee that meets weekly to provide daily support for the study. Any changes to the protocol will be notified to the ethics committee and an update will be made to the clinical trial record.

Participants who meet the eligibility criteria will be randomly allocated and balanced in a 1:1:1:1 ratio to one of the four groups, namely:
IPC-total occlusion pressure (TOP) [IPC-TOP]: this group will carry out baseline assessments, perform IPC using exactly the TOP, then perform post-IPC assessments and start EE. Post-exercise assessments will take place immediately after the end of EE and will be repeated at 24 h, 48 h, 72 h, and 96 h. All steps take place immediately after the end of the previous step, with the exception of the 24 h, 48 h, 72 h, and 96 h steps.IPC-40%: this group will perform baseline assessments, perform IPC using 40% higher pressure is to be applied than the closure pressure, then perform post-IPC assessments and start EE. Post-exercise assessments will take place immediately after completion of the EE and will be repeated at 24 h, 48 h, 72 h, and 96 h. All steps take place immediately after the end of the previous step, with the exception of the 24 h, 48 h, 72 h, and 96 h steps.IPC-10 mmHg: this group will carry out baseline assessments, perform the occlusion-perfusion intervention with 10 mmHg restriction characterizing the placebo, and then perform post-IPC assessments and start EE. Post-exercise assessments will take place immediately after completion of the EE and will be repeated at 24 h, 48 h, 72 h, and 96 h. All steps take place immediately after the end of the previous step, with the exception of the 24 h, 48 h 72 h, and 96 h steps.CONTR: this group will carry out the baseline assessments, and immediately afterwards start the EE. Post-exercise assessments will take place immediately after the end of the EE and will be repeated at 24 h, 48 h, 72 h, and 96 h. All steps take place immediately after the end of the previous step, with the exception of the 24 h, 48 h, 72 h, and 96 h steps.

There will be no special criteria for discontinuing or modifying the allocated interventions.

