### Placebo preconditioning

Placebo preconditioning will be performed on the dominant thigh with the same cuff, similar to the IPC protocol described above (Fig. 3), but with four cycles of 5 min of placebo occlusion (10 mmHg), alternating with four cycles of 5 min of reperfusion (0 mmHg) [38, 39].

It should be mentioned that in the three study groups, participants will be previously informed that the applied occlusion pressure will be sufficient to improve performance and avoid muscle damage. In addition, all procedures will be performed individually, to prevent participants from talking to each other about the compression generated by the cuff.

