### Strengths and weaknesses of the study

A strong point of the study is the comparison between two different IPC protocols with a placebo group and a control group, thus making it possible to observe the true results found from each intervention. The fact that the technique uses only a pressure cuff makes it easy to apply and access, so that it can be implemented in prevention and rehabilitation centers. Another positive point of the study is the monitoring of the effects of the technique for up to 96 h after the intervention, in addition to the high methodological quality of the study characterized by prospective registration, randomization, blinding, and intention to treat approach. However, a limitation of the study is the fact that the therapist and participants are not blind. Finally, some participants may be injured due to the strenuous protocol of eccentric exercise performed.

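### The protocol says participants know their allocation but describes a placebo procedure that needs them not to; effort-based and self-reported outcomes depend on which holds

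*Protocol article*

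**What the plan says.** All of this is in the protocol article.

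- The first Study design section: "This is a single-blind, placebo-controlled, clinical trial, with four parallel groups".
- Randomization, giving the nature of the interventions as the reason: "the participants who perform the exercise will not be blind to the allocation of the groups". The same section names who is masked: "There will be blinding of the evaluators and statistical analysis procedures".
- Placebo preconditioning: "in the three study groups, participants will be previously informed that the applied occlusion pressure will be sufficient to improve performance and avoid muscle damage". It adds that "all procedures will be performed individually, to prevent participants from talking to each other about the compression generated by the cuff".
- Strengths and weaknesses of the study: "a limitation of the study is the fact that the therapist and participants are not blind". The same paragraph lists blinding among the strengths and says that having a placebo and a control group lets the true effect of each intervention be seen.

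The control group goes straight from baseline assessment to the eccentric exercise, with no cuff procedure (group descriptions under Randomization). The primary outcomes are CK, blood lactate, MVIC and muscle thickness. Pain, pain threshold and perceived recovery are secondary. Statistical analysis compares all four groups in one repeated-measures ANOVA with post-tests and gives no contrast priority.

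**The concern.** A sham cuff controls for expectation only if its recipients do not know that it is the sham. The placebo section is written as if that were so. Randomization and the Discussion say that participants are not blind to their group. Staff running the sessions cannot tell from the text whether to withhold the arm.

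The outcomes at stake are those the participant produces. MVIC needs a voluntary maximal effort. Pain on the VAS, pressure pain threshold and perceived recovery are reported or signalled by the participant. Masked evaluators do not protect any of these from the participant's own belief.

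The contrast with control has a further problem. The promise of benefit concerns an applied pressure, and the control group has none. A difference between a cuff group and control on these outcomes may therefore reflect the promise as well as the occlusion.

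**Working it through.** **Step 1. Who is covered by the non-blinding statement?** It refers to participants who perform the exercise. All four groups perform it, so read plainly it includes the three cuff groups.

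**Step 2. Who receives the message?** Three groups of four. Control has no cuff, so by context these are IPC-TOP, IPC-40% and the 10 mmHg placebo. That control receives no promise of benefit is an inference; the article does not say so outright.

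**Step 3. What does each reading imply for the exposed outcomes?**

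| Reading | IPC versus 10 mmHg placebo | Any cuff group versus control |
|---|---|---|
| Arm disclosed to all participants | Same message, but expectation cannot be assumed equal | Expectation mixed with treatment |
| Participants know only cuff or no cuff | Largely protected, subject to step 4 | Expectation mixed with treatment |

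The first contrast depends on how the conflict is resolved. The second does not.

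**Step 4. How far can masking work?** The second Study design section places the TOP test in the first session, before baseline assessment, and exempts no group. The thigh cuff is inflated until the pulse disappears (Total occlusion pressure determination). The same cuff is then used for IPC and placebo (Ischemic preconditioning protocol; Placebo preconditioning). Each cuff participant has thus just felt full occlusion and can compare it with what follows. Keeping participants away from each other does not address this.

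**Step 5. Illustration of size.** The document gives no figure for an expectation effect, so the shifts below are assumptions. Take no true IPC effect, n = 20 per arm (80 participants in four groups), and a two-sided 5% t-test with 2 × 20 − 2 = 38 degrees of freedom. A spurious shift of d standard deviations gives noncentrality d × √(n/2) = d × √10:

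- d = 0.2: 0.2 × 3.162 = 0.632, rejection probability 0.095
- d = 0.3: 0.3 × 3.162 = 0.949, rejection probability 0.152
- d = 0.4: 0.4 × 3.162 = 1.265, rejection probability 0.234

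With the 16 per arm of the sample calculation (30 degrees of freedom), d = 0.2 and d = 0.4 give 0.085 and 0.195. The planned analysis is a four-group repeated-measures ANOVA with post-tests, so these are not error rates of this trial. They show only that a modest shift in belief would matter at this sample size.

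**The case against.** The strongest reply is that the two passages can be read together. The article attributes non-blinding to the nature of the interventions, which may mean only that people can tell whether they have a cuff. Participants would then know their procedure but not which pressure is the sham, and the common message would do its job of equalising expectation between IPC and placebo. This reading is possible and would largely protect that contrast. But neither the Randomization statement nor the Discussion limits itself in that way, so the text needs to say it.

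Other replies also have force:

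- A reader might infer that placebo participants are told they are receiving a 10 mmHg sham. No passage says so.
- A reader might take the single-blind label as a contradiction in itself. It is not: the masked parties named are the evaluators and the analysis, and single-blind can mean assessor-blind.
- An untreated control always differs in expectation from a treated group, and the placebo group is there to absorb that difference. This is true, and it is why claims on the exposed outcomes should rest on the placebo contrast. The analysis section does not give it that role.
- The lack of blinding is disclosed as a limitation. That deserves credit, but the disclosure neither mentions the unequal message nor reconciles the placebo section.
- Three of the four primary outcomes are laboratory or imaging measures, and the sample size rests on CK.

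**Conclusion.** The concern holds in a limited form. The statements on participant blinding conflict with the placebo procedure and must be reconciled. If allocation is disclosed, the 10 mmHg group cannot be relied on to control expectation for MVIC, pain, pain threshold and perceived recovery. Whichever reading is right, contrasts with control on those outcomes mix treatment with an induced expectation, provided, as inferred, that control participants get no comparable message. For them, the Discussion's claim that the design shows the true effect of each intervention is too strong.

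A reader might go further and conclude that the placebo group fails altogether. The documents do not support that: disclosure of the arm is one reading, not an established fact, and CK, lactate and muscle thickness are much less exposed to belief. Nor can the bias be quantified; the 9%, 15% and 23% rest on assumed shifts in a simplified two-arm test.

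**What to change.** 1. Reconcile Randomization, Placebo preconditioning and the Discussion. If this is what is intended, state that the three cuff groups are told neither their arm name nor their pressure, and that participants know only whether they have a cuff.
2. Keep the expectation wording identical across the three cuff groups.
3. For MVIC, pain, pain threshold and perceived recovery, base efficacy claims on IPC versus the 10 mmHg placebo. Label the contrasts with control on these outcomes as unblinded and soften the Discussion's claim accordingly.
4. Add a short arm-guess or expectancy question, so that masking is checked rather than assumed.
5. State as a limitation that every participant feels full occlusion with the same cuff in the TOP test on the same day, so masking will be imperfect.

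The cost is small: a script change, an ethics notification and a short question. The article reports recruitment as under way. If the script can no longer be changed, the reconciliation, the masking question for remaining participants and the restricted claims are still feasible.
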